## 2.3 Study Population

The study population comprises full-time female college teachers aged 25-59 years, employed in government colleges in Hyderabad district.

## 2.4 Study Duration

The study will be conducted from September 2024 to January 2025.

## 2.5 Sampling Strategy

### 2.5.1 Sample Population

The sample will consist of college teachers aged 25-59 years from government colleges in Hyderabad district.

### A. Inclusion Criteria:

**For Colleges**

Willing to participate in the study.

**For Teachers**

Full-time faculty members appointed in government colleges in Hyderabad district.

Aged between 25-59 years.

willing to participate in the study.

### B. Exclusion Criteria:

**For Colleges**

Colleges are unwilling to participate despite meeting inclusion criteria.

Colleges that participated in initial phases of the study, pilot testing, or cross-sectional studies.

**For Teachers**

Pregnant or lactating teachers.

Teachers on sabbatical leave.

Diagnosed/recovered breast cancer patients.

Teachers are unwilling to participate in the study.

### 2.5.2 Sampling Frame

A comprehensive list of government colleges in Hyderabad district.

A complete list of teachers employed in government colleges in Hyderabad district, including their names and employment ID numbers obtained from the relevant department.

### 2.5.3 Sampling Unit

Each female teacher employed in government colleges.

## 2.6 Sample Size Calculation

The sample size was determined for a cluster randomized controlled trial with considerations for an average cluster size of 99, an intra-cluster correlation coefficient (ICC) of 0.02, and a 20% attrition rate. The final required sample size adjusted for eligibility proportion was approximately 114 teachers, with 57 participants allocated to each group (intervention and control). Refer Appendix II.

## 2.7 Sampling Methods

A cluster sampling method will be applied, four colleges will be included in CRCT.A thorough eligibility assessment will be conducted. This evaluation will consider factors including the availability of an adequate number of qualified teachers, infrastructure needs, and study participation readiness. In the proposed research study, the following process will be followed to select a representative sample and conduct randomization for the cluster randomized trial.

**Step 1:**

**Block randomization.**

In this study, we will use a block randomization approach to allocate the four participating colleges into two balanced blocks of block size 2, for our cluster randomized controlled trial. The allocation of colleges to the intervention and control groups will be based on the total number of teachers in each college, aiming to achieve balance and minimize potential biases. For instance, the allocation resulted in the following distribution:

Block 1: 200 teachers

- College A (112)
- College B (88)

Block 2: 198 teachers

- College C (117)
- College D (81)

Each block will be designed to have almost the same total number of teachers from different colleges, ensuring that the allocation will be as balanced as possible given the available information. This approach will be chosen to enhance the validity of our trial by reducing the impact of variations in college sizes on the study's outcomes.

**Step 2:**

**Randomize Within Blocks:**

- Each block will be randomly assigned to one of the treatment groups. For example, flip a coin or use a random number generator to determine whether Block 1 goes to the intervention or control group, and similarly for Block 2.

**Required sample size:** The Total sample size required for the second phase of study is 114, that is 57 participants in each arm.

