**Study Design:**

A single blinded, cluster randomized controlled trial (cRCT) will be carried out among female college teachers from government colleges in Hyderabad district. Colleges will serve as randomization units (clusters). The study will proceed through three phases:

**Baseline Data Collection:** Data will be collected from both control and intervention groups.

**Intervention Delivery**: The intervention will be administered to the intervention group during this phase.

**Follow-up Data Collection**: Follow-up data will be collected at two different post-intervention points: one month and three months later. The same questionnaire will be used for both control and intervention groups. The intervention module will be applied to the control group after the study's completion.

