**Step 4: Proportionate Stratified sampling:**

Proportionate stratified sampling from all colleges based on faculty will be performed once the assignment of colleges is done to the intervention and control group, e.g., 2 colleges in the intervention group.

To calculate the proportions for each faculty within the intervention group (57) for the two colleges (A & B), these steps can be followed.

Proportions will be calculated based on the number of teachers in each faculty at each college.

e.g.

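### Step 2 assigns whole two-college blocks to arms, so only one unit per arm is randomised although colleges are the declared units

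*Combined protocol and SAP*

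**What the plan says.** - **Unit.** The Study Design section states: "Colleges will serve as randomization units (clusters". Section 2.7 adds that "four colleges will be included in CRCT".
- **Step 1 (Block randomization).** The plan is to "allocate the four participating colleges into two balanced blocks of block size 2". The grouping rule is size: "Each block will be designed to have almost the same total number of teachers from different colleges". The illustration puts A (112 teachers) and B (88) in Block 1, and C (117) and D (81) in Block 2.
- **Step 2 (Randomize Within Blocks).** "Each block will be randomly assigned to one of the treatment groups". By way of example, a coin or random number generator is used "to determine whether Block 1 goes to the intervention or control group, and similarly for Block 2".
- **Steps 3 and 4.** Step 3 labels A and B the intervention arm and C and D the control arm, with 57 teachers in each. Step 4 speaks of "e.g., 2 colleges in the intervention group".
- **Analysis and sample size.** The Data Summarizing and Analysis section plans GEE for correlation within colleges, with group, time and group-by-time effects. It does not mention blocks. Appendix II applies a design effect with an average college size of 99 and an ICC of 0.02.

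No section describes a draw of one college against another inside a block.

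**The concern.** The heading of Step 2 and the declared unit both promise that colleges are randomised. The procedure randomises blocks. A block normally serves to compare treatments inside it; here both members always receive the same treatment, so the block becomes the cluster.

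With one such unit per arm, whatever distinguishes A and B together from C and D together is fully confounded with the intervention. No block term can be fitted, because it would coincide with the group term. Variation between the two colleges inside an arm measures the error of the comparison only if colleges in the same block are no more alike than colleges in different blocks. The GEE and the design effect both proceed as if each college had been allocated separately. No later analysis can repair this, so it has to be settled before the draw.

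**Working it through.** **1. The plan's own figures.** Block totals: 112 + 88 = 200 and 117 + 81 = 198, as stated. Average college size: (200 + 198)/4 = 99.5 (the plan uses 99). Design effect: 1 + 98 × 0.02 = 2.96, and 28 × 2.96 = 82.88, rounded to 83. Then 83/0.8 = 103.75 (the plan carries 103) and 103/0.9 = 114.4, giving 114, or 57 per arm. The cluster in this calculation is the college.

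**2. What the size rule leaves to chance.** Four colleges can be divided two against two in three ways:

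| Split | Teachers | Difference |
|---|---|---|
| {A,B} v {C,D} | 200 v 198 | 2 |
| {A,D} v {B,C} | 193 v 205 | 12 |
| {A,C} v {B,D} | 229 v 169 | 60 |

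Near-equal totals select the first row. Chance then decides only which side is called intervention.

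**3. Number of allocations and smallest attainable randomisation p-value.** With K equally likely allocations that include their mirror images, the minimum is 1/K one-sided and 2/K two-sided.

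| Scheme | K | One-sided | Two-sided |
|---|---|---|---|
| One block per arm (intended reading) | 2 | 0.50 | 1.00 |
| One draw in each of two pairs | 4 | 0.25 | 0.50 |
| Any two of four colleges | 6 | 0.17 | 0.33 |

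**4. Literal reading of Step 2.** Two independent fair flips give four outcomes, each with probability 0.5 × 0.5 = 0.25. No control arm: 0.25. No intervention arm: 0.25. One arm empty: 0.25 + 0.25 = 0.50.

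**5. Type I error if blocks differ.** The documents give no block-level correlation, so it is assumed and varied. Settings: no intervention effect; prevalence 0.26 (the control figure in Appendix II); college ICC 0.02; analysed colleges of 22, 19, 25 and 17 teachers (total 83, the number before inflation for attrition and eligibility); t-test on college proportions with 2 df; 40,000 simulated trials; nominal level 5%.

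| Shared feature | Assumed ICC | Whole blocks to arms | Pairs A/C and B/D |
|---|---|---|---|
| None | 0 | 4.9% | 5.1% |
| A with B, C with D | 0.02 | about 8% | about 6% |
| A with B, C with D | 0.05 | about 12% | 7–8% |
| A with B, C with D | 0.10 | about 18% | 10–11% |
| A with C, B with D (follows size) | 0.02 / 0.05 / 0.10 | 4.1 / 3.3 / 2.6% | 4.0 / 3.3 / 2.6% |

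The last column can be checked by hand for the A-with-B scenario. Half the paired draws recreate {A,B} v {C,D}; the other half split each of those blocks across arms, where type I error is 4.2%, 3.5% and 2.6%. The averages are (7.9 + 4.2)/2 = 6.1%, (12.5 + 3.5)/2 = 8.0% and (18.3 + 2.6)/2 = 10.5%.

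**6. Which pairing.** Applying the Step 2 heading to the existing blocks (A against B, C against D) gives 229 v 169 in half the draws and 205 v 193 in the rest. Pairing by size (A against C, B against D) gives only 200 v 198 or 193 v 205.

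**The case against.** The case for the plan has four parts.

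- **Two filled arms are intended.** A reader might infer from Step 2 that the trial has an even chance of losing an arm. The flip is offered only as an example, the same step requires 57 per arm, and Steps 3 and 4 fill both arms. The documents support no more than an unstated constraint. Even taken literally, losing the control arm has probability 0.25; the 0.50 covers either arm.
- **The grouping is not arbitrary.** Step 1 states a size criterion, and it picks one split without discretion. With opposite assignment each college still has a 50% chance of either arm. This stands, and it means that calling the blocks hand-picked would overstate the matter. It does not restore the college as the randomised unit.
- **Nothing says A resembles B.** This also stands. With no shared block feature the error rate is nominal, and if the feature follows college size the present grouping already places similar colleges in opposite arms. The inflation is conditional. The confounding and the count of allocations are not.
- **The remedy is modest.** A reader might infer that it brings type I error down to about 4%, 3% and 3%. Those rates belong to always splitting A from B and C from D, which the size pairing does in only half its draws.

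**Conclusion.** The contradiction is established from the text alone: the declared unit and the Step 2 heading say colleges within blocks, while the procedure and Step 3 use whole blocks as arms. On the reading most favourable to the plan, one unit per arm is randomised, two allocations exist, and block and intervention effects cannot be told apart. That conclusion needs no assumption.

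The effect on type I error does need one. It is about 8% to 18% if colleges within a block share a feature with ICC 0.02 to 0.10, and nominal or below in the other scenarios examined. The documents do not show which case applies, so they do not support a claim that the test is inflated as a matter of fact. The missing one-block-per-arm constraint is a secondary drafting gap.

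The wording must be corrected before allocation. Doing so does not remove the larger limit of four colleges: about 2 between-college degrees of freedom, and a two-sided randomisation p-value that cannot fall below 0.50.

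**What to change.** Replace the Step 2 instruction with wording to this effect: *The four colleges are paired by number of teachers (A with C, B with D). For each pair, one documented computer-generated draw assigns one college to intervention and the other to control.* Amend Step 1 so that it forms these size-matched pairs rather than blocks with equal totals.

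This yields four allocations, always two colleges per arm, and totals of 200/198 or 193/205. {A,B} v {C,D} can still occur, but by chance.

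Recompute the Step 3 quotas after the draw. For {A,D} v {B,C}:

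- A: 112/193 × 57 = 33.1; D: 81/193 × 57 = 23.9 (33 and 24)
- B: 88/205 × 57 = 24.5; C: 117/205 × 57 = 32.5 (24 and 33, from 24.47 and 32.53)

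The printed quotas for A and B need a check in any case: 112/200 × 57 = 31.9 and 88/200 × 57 = 25.1, against 31 and 26.

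State in the analysis section whether the pairing enters the model. A paired comparison leaves 1 df (critical t 12.71), an unpaired one 2 df (4.30).

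The cost is protocol wording before allocation. The colleges and the 114 teachers stay the same.

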**Step 3: Calculation of Proportions and allocated sample size for Each College:**

**Intervention Arm**

1. College A= (112) - 112/ 112+88*57=31
2. College B = (88)- 88/112+88*57=26

**Control Arm**

1. College C (117) - 117/117+81*57=34
2. College D (81) 81/117+81*57=23

**Step 4: Proportionate Stratified sampling:**

Proportionate stratified sampling from all colleges based on faculty will be performed once the assignment of colleges is done to the intervention and control group, e.g., 2 colleges in the intervention group.

To calculate the proportions for each faculty within the intervention group (57) for the two colleges (A & B), these steps can be followed.

Proportions will be calculated based on the number of teachers in each faculty at each college.

e.g.

**College A=Total number of teachers= 112**

Arts: (52 / 112) *31 =14 participants

Science: (49/ 112) * 31 = 14 participants

Commerce: (11/ 112) * 31 = 03 participants

**2. College B: Total number of teachers=88**

Arts: (40 / 88) * 26 = 12 participants

Science: (37 / 88) * 26 = 10 participants

Commerce: (11 / 88) * 26= 4 participants

Similarly stratified proportionate sampling will be done for the Colleges of Control group.

**Step 5 Random sampling:**

Participants will be selected randomly by random number generators, randomly selected participants will be invited for the study, exclusion and inclusion criteria will be discussed; written consent will be obtained from eligible participants, and baseline data will be collected.

[figure not shown]

Figure III. CONSORT flow diagram of the study—adapted from Campbell (Campbell, Elbourne, & Altman, 2004)

## 2.8 Study outcomes

**2.8.1 Primary outcome**

The primary outcome for this study is the practice of Breast Self-Examination (BSE). This will be assessed based on the percentage of participants who consistently and effectively perform breast self-examinations. Participants will self-report on their BSE practices using a structured questionnaire. Regular BSE practice will be defined as performing the examination once a month, while any other response indicating irregular BSE will be categorized as non-practicing.

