## 2.16 Operational Definitions of Variables

**13.15.1 Dependent Variables**

**1. Practice of Breast Self-Examination (BSE)**

- **Frequency of BSE:** Participants will be categorized as practicing BSE regularly (once a month or more) or irregularly (occasionally or less).
- **Performance of BSE:** Participants will be assessed on their knowledge of how to conduct BSE through a series of questions.

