**SECTION IV: PRACTICE**

**BSE Practice**

1. Do you practice BSE regularly to check for any changes or abnormalities in your breasts?

- Yes
- No

2. Which best describes the frequency of your Breast Self-Examinations (BSE)?

- Never
- Once in a month
- Once in a three-month period.
- Once in a six-month period.

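### The primary endpoint is worded inconsistently, its questionnaire item has no recall period, and no primary visit is named, so at month 1 a single examination cannot be told from a monthly habit

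*Combined protocol and SAP*

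**What the plan says.** **Definition.** Section 2.8.1 describes the primary outcome as the "percentage of participants who consistently and effectively perform breast self-examinations" and then gives the scoring rule: "Regular BSE practice will be defined as performing the examination once a month", with any other answer that indicates irregular practice counted as not practising. Section 2.16 (Operational Definitions of Variables) classes teachers as "practicing BSE regularly (once a month or more) or irregularly (occasionally or less"). It adds a performance component that is scored as knowledge: "Participants will be assessed on their knowledge of how to conduct BSE through a series of questions".

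**Instrument.** Section IV of the questionnaire has two practice items. Item 1 is a Yes/No question on practising regularly, with that word left undefined. Item 2 asks "Which best describes the frequency of your Breast Self-Examinations (BSE") and offers four answers: never, once in a month, once in three months, once in six months. Neither item states a recall period. Nothing says which item is the endpoint, or what happens when they disagree.

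**Timing.** The Study Design section states: "Follow-up data will be collected at two different post-intervention points: one month and three months later". Section 2.14 reuses the baseline form at follow-up without its first section, so the practice items are identical at baseline, month 1 and month 3.

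**Analysis.** Data Summarizing and Analysis lists chi-square or Fisher tests for categorical comparisons and a GEE with group, time and group-by-time effects. It fills missing values with the participant's last recorded one. No visit or contrast is designated primary.

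**The concern.** The practice of breast self-examination (BSE) is the trial's only primary outcome, and the intention is to show a sustained habit. One month after the session, a teacher who examined herself once has done so once in that month. The matching answer is the one that scores as regular practice. A teacher with a true monthly habit gives the same answer.

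The ambiguity would not fall evenly on the two arms. Under section 2.12 the intervention arm receives hands-on training on a model, a video, reminder objects and WhatsApp messages for three months. The control arm receives nothing until the last follow-up is complete. One-off attempts prompted by the session would therefore occur mostly in the intervention arm.

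With no primary visit or contrast named, the headline result could rest on the visit where the item is least able to show what the objective asks for. A teacher who drops out after month 1 also has her month-1 answer carried to month 3.

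**Working it through.** **1. The plan's own figure.** Appendix II uses P1 = 85.6%, P2 = 26%, z-values 1.96 and 0.84. The mean proportion is (0.856 + 0.26)/2 = 0.558.

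n per arm = [1.96·√(2 × 0.558 × 0.442) + 0.84·√(0.856 × 0.144 + 0.26 × 0.74)]² / 0.596² = 9.62, so 10. With continuity correction it is 13. The plan states 14, which is close enough.

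Then 28 × (1 + 98 × 0.02) = 82.88, so 83; 83/0.8 = 103.75; 103.75/0.9 = 115.3. Rounding up at each step gives 116; the plan rounds down to 114. The stated size reproduces within tolerance, and this point does not alter that calculation. P1 and P2 are, however, rates of regular practice six months after intervention, whereas follow-up here ends at three months.

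**2. How item 2 scores under each section.**

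| Item 2 answer | Section 2.8.1 | Section 2.16 |
|---|---|---|
| Never | not regular | not regular |
| Once in a month | regular | regular |
| Once in three months | not regular | not regular |
| Once in six months | not regular | not regular |

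The two wordings give the same result for every available answer. They differ only for a teacher who examines more often than monthly, and the form has no box for her. If she ticks *Once in a month*, nothing is lost. If such teachers are instead lost as non-regular, at assumed rates of 10%, 20% or 30% of true practisers in both arms, the planned 59.6-point difference shrinks by that fraction to 53.6, 47.7 or 41.7 points.

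**3. One-off attempts at month 1.** The documents give no misclassification rate, so f is assumed: the share of truly non-regular intervention teachers who tick *Once in a month*. Suppose there is no true effect, both arms are at 26%, and controls are unaffected. The observed intervention rate is 0.26 + 0.74f:

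| f (assumed) | Observed intervention | Control | Spurious difference |
|---|---|---|---|
| 10% | 33.4% | 26% | 7.4 points |
| 25% | 44.5% | 26% | 18.5 points |
| 50% | 63.0% | 26% | 37.0 points |

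**4. What carry-forward passes to month 3.** Take the plan's 20% attrition and assume that all of it falls between months 1 and 3, that dropouts misreport at the same rate as others, and that month-3 answers are otherwise correct. The month-3 distortion is then 0.20 × 0.74f = 1.5, 3.7 or 7.4 points. It is smaller than at month 1 but runs in the same direction.

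**The case against.** Much can be said for the plan. The answer *Once in a month* maps directly onto the frequency rule in section 2.8.1. Item 2 asks for the frequency that best describes the teacher's examinations, which reads as a question about habit. The analysis section specifies a longitudinal model rather than a separate test at each visit. Section 2.10 provides for expert and participant review, with revision, before the questionnaire is used.

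These arguments rule out several stronger readings that a reader might infer:

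- *The item cannot measure either definition.* It can measure monthly frequency. It cannot record more-than-monthly practice, consistency over a stated period, or effectiveness.
- *The same teacher succeeds under one section and fails under the other.* The table in step 2 shows that no available item 2 answer does this. Section 2.8.1 excludes only responses that indicate irregular practice, so it need not exclude more frequent examination.
- *The plan scores one attempt as regular practice.* No rule says so. It follows only as a possibility from the missing recall period.
- *Two items at two visits make four primary tests, with a familywise error of 1 − 0.95⁴ = 18.5%.* The documents do not make the Yes/No item an endpoint, the GEE covers the whole study period, and answers from the same teachers would not be independent.

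What remains is not answered. A habit question without a time frame, put one month after training, does not separate a first attempt from a habit. The validation steps do not set a recall period, choose the endpoint item or name a primary contrast.

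**Conclusion.** The point holds as an endpoint-definition and measurement problem. The wording should be reconciled, but the mismatch alone changes no score. The substantive defects are the missing recall period, the lack of a rule for the two items, the unnamed primary visit and contrast, and an effectiveness element that Section IV does not measure.

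The likely direction of bias is towards the intervention, mainly at month 1 and to a lesser extent at month 3 through carry-forward. The size is unknown. The 7.4 to 37.0 points at month 1, and 1.5 to 7.4 points carried to month 3, show sensitivity to assumed rates and are not estimates. They also assume no comparable over-reporting in the control arm. As it stands, a month-1 percentage could not be read as sustained monthly practice.

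**What to change.** Before the questionnaire is pretested:

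1. Use one definition in sections 2.8.1 and 2.16: at least once a month, with more frequent examination counted as regular.
2. Base the endpoint on the frequency item alone. Reword it with a stated recall period, for example in how many of the last three months BSE was done, and ask it identically at baseline and month 3. Fix the cut-off for regular practice in advance. Requiring all three months is one option among several.
3. Name the month-3 between-group contrast from the GEE as primary.
4. Make month 1 secondary, as any BSE since the last questionnaire. Do not carry it forward as regular practice, and state how missing month-3 answers will be handled.
5. Drop effectiveness from the endpoint, or state how it is measured.

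**Cost.** The change is one reworded item and some aligned text. Once baseline data exist, changing the item breaks comparability with baseline, so timing matters.

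The larger cost is to the planning assumptions. Observed rates will probably be lower and will no longer match 85.6% versus 26%. The sample size section should say that the stated 80% power rests on those rates, which are six-month figures under another definition. As an illustration with assumed rates and no continuity correction, 50% versus 26% needs about 63 per arm before inflation, and 50% versus 10% about 19.4. The plan's own inflation, 2.96/(0.8 × 0.9) = 4.11, takes these to about 259 and 80 per arm, against the planned 57.
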